## Abstract

**Introduction:**

Depression is one of the most common psychological disorders in later life. Although psychological interventions are recommended by treatment guidelines, most older adults with depression remain untreated. The aim of this study is to evaluate the efficacy of the Portuguese version of Metacognitive Training for Depression in later life (MCT-Silver).

**Methods:**

This is a study protocol of an observer-blind, parallel-group, randomized controlled trial to compare the efficacy of MCT-Silver with a treatment as usual (TAU) control group among older adults (age 65 years and older) with depressive symptoms according to the Montgomery-Asberg Depression Scale. Participants will be tested at three assessment time points (baseline, immediately following the intervention [8 weeks], and 3 months after the intervention). The primary outcome is change in self-rated depression symptoms assessed by the Beck Depression Inventory (BDI-II). Secondary outcomes include clinician-rated depression, self-esteem, dysfunctional beliefs, metacognitive beliefs, ruminations, attitudes toward aging and quality of life. A self-designed subjective appraisal rating scale consisting of 21-items will be used to assess participant acceptance of MCT-Silver.

**Discussion:**

MCT-Silver is an innovative intervention, which aims to reduce dysfunctional thoughts as well as depression-related behaviors and coping strategies through the metacognitive perspective. Until now, the training has only been tested in Germany. It is expected that after 8 weeks of treatment and 3 months later, the experimental group will demonstrate significant reductions in depressive symptoms, metacognitive beliefs, dysfunctional attitudes and ruminative responses compared to the TAU group. Moreover, quality of life, self-esteem, and attitudes towards aging will be significantly improved in MCT-Silver compared to the TAU group.

**Clinical trial registration:**

ClinicalTrials.gov, NCT05640492.

## Introduction

1.

According to the World Health Organization, depression is a common mental disorder, with around 280 million people diagnosed with the condition worldwide (World Health Organization, 2021). In 2019, depression was estimated to affect around 10.4% of adults, reaching about 5.7% in people over 60 years old (World Health Organization, 2021). In addition, depression is one of the main causes of years lived with disability (James et al., 2018; Santomauro et al., 2021) and it has been identified as a cause of dementia in older adults (Wu et al., 2020).

Depression is a mental disorder that can be manifested by persistent sadness, hopelessness, pessimism, loss of pleasure or interest in activities, and depressed mood (e.g., sad, irritable, empty). This symptomatology is present during most of the day, almost every day, for at least 2 weeks and most episodes can last considerably longer (American Psychiatric Association, 2014). Over time, depression can lead to cognitive and social dysfunction. It is therefore important to intervene as early as possible in order to minimize or eliminate disabilities and improve quality of life (Pinho et al., 2021).

The treatment of depression with antidepressant monotherapy is still a reality due to limited resources for treatment in community health centers or psychosocial rehabilitation facilities, but is limiteddue to side effects of medications, polypharmacy and poor adherence (e.g., due to memory impairment or organizational deficits). Given that rate of relapse after discontinuation of antidepressant medication reaches 56% (Kishi et al., 2023), implementation of psychotherapeutic strategies in the development of care management plans for depression is necessary. Moreover, the pharmaceutical treatment of depression is insufficient for the full rehabilitation of patients (Carvalho Pereira de Melo and Pereira de Melo, 2021; Mommaerts, 2022).

Metacognitive training for older adults with depression (MCT-Silver; Schneider et al., 2018; Bücker, 2019), is a cognitive-behavioral (CBT)-based group intervention, specifically designed for adults ages 60 years and older (all materials are available for free^1^). MCT-Silver aims to reduce the treatment gap by improving access to mental health care for the estimated 73% of older adults with depression who go untreated (Horackova et al., 2019). MCT-Silver is based on metacognitive training for psychosis (MCT; Moritz and Woodward, 2007) and metacognitive training for depression (D-MCT; Jelinek et al., 2015). Randomized controlled trials on D-MCT provide evidence for its efficacy on depressive symptoms (Jelinek et al., 2016), as well as metacognitive and negative cognitive beliefs (Hauschildt et al., 2022; Özgüç and Tanriverdi, 2022) at short- and intermediate follow-up intervals. Long-term efficacy of D-MCT remains equivocal (Jelinek et al., 2019). A pilot study examined the feasibility, acceptance, and effects of D-MCT as an add-on intervention in a group of older adults with depression who were completing an intensive inpatient treatment program (55+ years; *N* = 116). Per protocol analyses (*n* = 55) yielded a significant decrease in depressive symptoms (*d* = 1.06) and cognitive biases (*d* = 0.33). These results support the feasibility and acceptance of D-MCT among older adults with depression. A recently completed RCT in Germany, which compared MCT-Silver to an active control group (cognitive remediation; (Schneider et al., 2018)) yielded large and significant reductions on the primary outcome (Hamilton Depression Rating Scale) from baseline to post and 3-month follow-up (*d_MCT-Silver_* = 1.25 – 1.42; *d*_CR_ = 1.05 – 1.12). Group differences; however, did not reach significance (η_p_^2^ = 0.001 – 0.002). MCT-Silver yielded significant moderate to large effects compared to CR immediately following the intervention and after 3 months for self-reported depression (BDI-II: η_p_^2^ = 0.075 – 0.135) and rumination (RRS: η_p_^2^ = 0.087 – 0.127). A significant moderate effect was found for positive metacognitive beliefs (MCQ-PB) at post-assessment (η_p_^2^ = 0.067), but group differences did not reach significance at follow-up (η_p_^2^ = 0.027). Small reductions in negative cognitive beliefs (Dysfunctional Attitudes Scale-18B) at post- and at 3-month follow-up (*d_MCT-Silver_* = 0.24 – 0.30) were found for the MCT-Silver group, whereas negative cognitive beliefs were unchanged in the CR group (*d_CR_* = –0.06 – 0.06).

Like D-MCT, the main goal of MCT-Silver is to strengthen patients’ ability to reflect upon their thinking, and to recognize and correct their dysfunctional thought patterns and behavior (Moritz et al., 2018; Schneider et al., 2018) in order to ultimately reduce depressive symptoms. Additionally, MCT-Silver aims to increase awareness of depression-related information processing strategies, such as attentional preferences for negative information and mood-congruent memory (Blaney, 1986; Wittekind et al., 2014; McConnell and Troop-Gordon, 2021). Individual modules also address dysfunctional coping strategies (e.g., thought suppression, rumination) and metacognitive beliefs (e.g., rumination helps to solve problems). As a “modern” CBT-intervention, MCT-Silver includes third-wave elements drawn from acceptance and commitment therapy (Hayes et al., 2006) and imagery rescripting (Holmes et al., 2016). The training also addresses age-specific challenges and risk factors for depression in older adults (e.g., loneliness, functional limitations, loss of relationships).

MCT-Silver has not yet been validated for the Portuguese population and studies are needed to prove its efficacy in this population. Therefore, after the completion of a pilot study, a randomized controlled trial will be conducted to evaluate the efficacy of the intervention in older adults with depression. The research question of this study is as follows: “Does MCT-Silver in older adults with depression lead to a greater reduction in depressive symptoms and dysfunctional beliefs as well as improved metacognitive beliefs, quality of life, ruminative responses, self-esteem and attitudes towards aging compared to treatment as usual?.” The pilot study is in preparation. After completion of the pilot study and application of results as necessary (e.g., adjustment of MCT-Silver for the Portuguese population), we will continue with the intervention in order to finalise the RCT.

## Materials and methods

2.

### Aim

2.1.

The aim of this study is to evaluate the efficacy of MCT-Silver and its effects on depressive symptoms, dysfunctional beliefs, metacognitive beliefs, quality of life, ruminative responses, self-esteem and attitudes towards aging. The hypotheses that we want toexamine in this trial are the following:

Primary outcome: There will be a greater reduction in self-reported depression (as measured by the Beck Depression Inventory-II) for MCT-Silver vs. TAU (pre-post; pre-follow-up).Secondary outcomes: There will be a greater reduction in clinician-rated depression (MADRS), metacognitive beliefs (Metacognitions Questionnaire-30), self-reported depression (PHQ-9), dysfunctional beliefs (DAS-18B), ruminative responses (RRS), self-esteem (Self-Esteem Questionnaire), quality of life (WHO QOL-Bref??), and attitudes to aging (Attitudes to Aging Questionnaire) for MCT-Silver vs. TAU (pre-post; pre-follow-up).Tertiary outcome: Participants will rate the intervention positively on a satisfaction questionnaire administered after the 8-week intervention period.

### Design/methodology

2.2.

#### Study design

2.2.1.

This study represents an observer-blind, parallel-groups randomized controlled trial.

All procedures follow CONSORT (Consolidated Standards of Reporting Trials) guidelines and follow four phases: enrollment, intervention allocation, follow-up, and data analysis. The follow-up will occur 3 months after completion of the intervention. The trial has been registered at ClinicalTrials.gov (NCT05640492).

#### Participants

2.2.2.

The sample will be selected by a probabilistic method and participants will be randomly assigned to one of two groups (MCT-Silver vs. TAU) based on a randomized plan.

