#### Randomization and blinding

2.2.3.

Eligible participants will be recruited at each institution (the mental health service of each hospital that agreed to take part in the study in Portugal) through telephone contact by the researchers in collaboration with the multidisciplinary team. The study will also be publicized in the media so that older adults can contact the researchers if they are interested in participating. A baseline assessment will be carried out and all instruments will be applied after informed consent from participants. All participants who agree to participate in the study will be assigned a code and will be randomly assigned to either MCT-Silver (experimental group where the intervention will be applied) or the control group (no stratification factors). This randomization will be performed using a computer program. The control group will not be administered the intervention (MCT-Silver). In both groups, treatment will be maintained as usual (Treatment As Usual – TAU) and participation in other interventions as well as use of medications will be carefully monitored. Study participants will be informed that they should not reveal which group they are in and will be reminded of this at each testing session. All participants will be re-assessed at the end of the intervention and 3 months after completion, with the application of all planned instruments. Assessments will be performed by the same rater before and after the intervention and at follow-up. Assessors will be trained in the administration of all instruments prior to the start of the study. A third researcher will inform patients of group assignment so that raters will remain blinded throughout the study. The Side Effects of Intervention questionnaire and patient satisfaction with MCT-Silver will be applied to the experimental group post-intervention (Table 1; Figure 1).

**Table 1 tab1:** Study schedule.

	Study period				
	Enrolment	Randomization	Intervention (8 weekly sessions)	Post (8 weeks)	Follow-up (3 months)
TIMEPOINT	T-1	T0		T1	T2
Enrolment:					
*Eligibility screen*	X				
*Informed consent*		X			
*Randomization*		X			
Interventions:					
*Treatment As Usual (TAU)*	X	X	X	X	X
*MCT-Silver*			X		
Assessments: *Baseline*		X			
*Post-intevention*				X	
*Follow up*					X

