##### Treatment as usual

2.2.5.1.

All participants (experimental and control group) will continue to receive treatment as usual (TAU) at their institution. TAU may consist of psychiatric and psychosocial treatment by a multidisciplinary team, which includes mental health psychiatric nurses, psychiatrists, psychologists, social workers, occupational therapists and other mental health professionals. TAU may also include treatment in community settings, day hospital and inpatient settings, as well as antidepressant medication, psychosocial rehabilitation, socialisation groups and psychoeducational and therapeutic groups. The care of participants in TAU will not be limited or influenced in any way. To control for TAU, we will carefully record participation in concurrent treatment. The control group will not participate in the MCT-Silver programme.

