### Validity and reliability/rigour

2.4.

Variables such as educational level, duration of mental disorder, and type of treatment may influence the results of this study. The proposal to use the stratified random sampling method in this study aims to minimize confounding bias. All procedures, including the implementation of the intervention will be carried out after trainers have completed MCT-Silver training to minimize the risk of bias. Participants will be randomly allocated to either the experimental group [MCT-Silver + Treatment As Usual (TAU)] or the control group (TAU only). A computer-generated stratified random sampling method will be applied taking into consideration an equitable distribution by sex and age to promote sex and age equality and inclusiveness. Finally, all raters will be blinded to participant group assignment.

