## Discussion

3.

MCT-Silver is a low intensity, CBT-based group intervention, which appears to have great potential in reducing depressive symptoms but further studies are needed to better validate its efficacy as the pilot study was limited due to lack of a control group (Schneider et al., 2018) as well as the lack of follow-up assessments. Only one RCT on MCT-Silver has been conducted (in Germany) (Schneider et al., under review).^3^ The efficacy of MCT-Silver for older adults with depression has not yet been studied in the Portuguese population and, therefore, the development of the present trial is essential.

Portugal is one of the countries of the Organization for Economic Co-operation and Development (OECD) with the highest consumption of antidepressants (OECD, 2019) and, despite international guidelines recommending complementary treatment with non-pharmacological interventions (American Psychological Association, 2019), in Portugal this practice is not common. Most people with depression are only treated with medications.

It is expected that the results of this trial will provide support for the efficacy of the Portuguese version of MCT-Silver on the reduction of depressive symptoms. Moreover, it is anticipated that participants in the MCT-Silver group will demonstrate greater reductions in metacognitive beliefs, dysfunctional attitudes, ruminative responses and (negative) attitudes towards aging, as well as greater improvements in quality of life and self-esteem compared to a TAU group. The results of this trial are expected to allow future implementation of MCT-Silver by mental health and psychiatry professionals in various contexts. The MCT-Silver programme aims to contribute to the psychosocial rehabilitation of older adults with depression. The trial illustrated in this protocol intends to assess the efficacy of MCT-Silver in the Portuguese population.

Since people with depression often have cognitive deficits (Muhammad and Meher, 2021), patients with significantly impaired cognitive abilities may have difficulty understanding MCT-Silver exercises. To overcome this limitation, we will apply the MMSE to screen for cognitive deficits. Other limitations may be transportation difficulties getting to sessions regularly, as well as health problems, which may limit participation in the study or the changes in medication during the course of the study.

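### The sample is called probabilistic but is a volunteer sample, and usual care is not defined for self-referred participants who are not in treatment

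*Protocol article*

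**What the plan says.** On selection, the Participants section says: "The sample will be selected by a probabilistic method". The same sentence goes on to state random assignment to the two groups. Selection is therefore claimed as probabilistic in addition to random allocation. The Validity and reliability/rigour section uses related wording: "The proposal to use the stratified random sampling method in this study aims to minimize confounding bias".

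On recruitment, the Randomization and blinding section names two routes. The first is hospital services: "Eligible participants will be recruited at each institution (the mental health service of each hospital that agreed to take part in the study in Portugal", with telephone contact by the researchers. The second is self-referral: "The study will also be publicized in the media so that older adults can contact the researchers if they are interested in participating".

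On the comparator, the Treatment as usual section says: "All participants (experimental and control group) will continue to receive treatment as usual (TAU) at their institution". It lists a wide range of possible care and adds: "The care of participants in TAU will not be limited or influenced in any way". The section on MCT-Silver places the group sessions in a room of the group's own institution.

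On reach, the Discussion says: "The trial illustrated in this protocol intends to assess the efficacy of MCT-Silver in the Portuguese population".

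**The concern.** Two stated properties do not match the recruitment described.

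First, calling a sample probabilistic invites the reader to treat it as representative of a defined population. A sample of consenting hospitals and volunteers gives no such warrant.

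Second, the comparator is described as if every participant were already a patient somewhere. If people outside care can enrol, TAU covers anything from multidisciplinary hospital care to nothing. A result for MCT-Silver plus TAU against TAU is then harder to interpret. It may reflect an addition to active treatment, a contrast with no treatment, or a blend of the two in proportions set by who responds to the publicity.

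**Working it through.** The plan gives no figure on this point, so the main check is to set the sections side by side.

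**1. Is selection probabilistic?** A probability sample needs a frame and a known, non-zero chance of selection for each member of the target population. Here hospitals enter by agreeing, their patients by being contacted and consenting, and the remainder by choosing to contact the researchers. The article describes no frame, selection probability or weight, and the Data analysis section uses no sampling weights. Only allocation is random.

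**2. Must a participant have an institution or current care?**
- The five inclusion criteria concern age, MADRS score, capacity to consent, language and willingness. None concerns current care.
- None of the seven exclusion criteria removes people who are not in care.
- Table 4 accepts No for medication, psychiatric admission, day hospital and follow-up appointments.

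A self-referred person with no current treatment is therefore eligible. For that person, the statements that TAU continues at the institution and that sessions take place at the group's institution have no defined meaning.

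**3. What does the pooled estimate represent?** Let *p* be the share not in treatment, *a* the effect when added to active care, and *b* the effect against no care. Then

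pooled effect = (1 − *p*)·*a* + *p*·*b* = *a* + *p*·(*b* − *a*).

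The departure from a pure add-on effect is *p*·(*b* − *a*). It is zero if *p* = 0 or *a* = *b*. The documents give none of *p*, *a* or *b*, so no size follows from them.

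**4. Does the mix bias the comparison between arms?** This was simulated with assumed inputs: 16 per arm (the pilot's 32 divided equally), a constant true effect of −5, SD 9, a 4-point outcome shift by care status, and 20,000 replicates.

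| Share of self-referrals (assumed) | Mean estimate | SD of estimate |
|---|---|---|
| 10% | −4.99 | 3.21 |
| 25% | −4.99 | 3.23 |
| 50% | −4.97 | 3.27 |

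There is no systematic bias. The effect was held constant, so this run speaks to confounding between arms and not to the averaging in step 3.

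Chance imbalance is a separate matter. Under equal allocation, the hypergeometric probability that the arms differ by 20 percentage points or more in self-referral share is:

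| Per arm (assumed) | 10% self-referred | 25% | 50% |
|---|---|---|---|
| 16 | 0% | 22% | 29% |
| 50 | 0.1% | 2% | 7% |
| 100 | 0% | 0.2% | 0.7% |

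The zero at 16 per arm arises because 3 self-referrals can differ by at most 3/16 = 18.75 points. Imbalance matters mainly in a small trial, which is a modest argument for adjustment.

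**5. What is already recorded or planned?** Medication, type of treatment and follow-up programmes are among the baseline data. Concurrent treatment is to be recorded during the study. Previous or current treatment is a planned moderator of the primary outcome. Recruitment route is not listed, and the moderator as worded joins past with present treatment.

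**The case against.** The strongest reply is that these are wording mismatches with little consequence, and much of it stands.

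- A reader might infer that the TAU comparison fails. The documents do not support that. Participants from both routes are randomised, the mix is the same in both arms in expectation, and TAU is openly variable and unrestricted.
- A reader might infer that different kinds of background care are averaged without anyone being able to see it. That is also unsupported, because Table 4 and the monitoring of concurrent treatment capture care status, and a treatment moderator is planned.
- The Introduction's estimate that 73% of older adults with depression go untreated describes that population in general, not the people who answer this trial's publicity. Their number and care status are unknown and could be unimportant.
- No analysis depends on probability selection. The population statement in the Discussion can be read as a contrast with the earlier German trial.
- The phrase about stratified random sampling in Validity and reliability/rigour stands beside a computer-generated method balancing sex and age. It appears to describe allocation, so it should not be rewritten as a recruitment statement.

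What the reply does not remove is that the Participants section claims probabilistic selection separately from random assignment, and the recruitment described does not have that property. Nor does it supply a meaning of TAU or delivery site for someone without an institution.

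**Conclusion.** The point holds in a limited form. The sample is a non-probability, volunteer sample, and the description of it as probabilistic is incorrect. Generalisation to the Portuguese population must be argued on other grounds. Continued care at an institution is not assured for every participant, because eligibility does not require it.

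Internal validity is not affected. Interpretation and generalisability are: the estimate averages over background care and cannot be read purely as an addition to active treatment.

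No magnitude can be given. It would need the untreated share and the effects by care status, and the documents state neither. That some self-referred people will be outside care is an inference that the criteria and the baseline form allow, not something the protocol states.

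**What to change.** 1. In Participants, replace the probabilistic description with a non-probability one: patients of participating services and self-referred volunteers. Keep the word random for allocation only, and limit the generalisability statement in the Discussion to match.
2. Reconcile Randomization and blinding, Treatment as usual and the MCT-Silver section on what TAU and the delivery site mean for self-referred participants.
3. Add recruitment route to Table 4.
4. Derive current treatment (yes/no) from the baseline items already collected and enter it as a covariate in the primary ANCOVA.
5. Split the planned treatment moderator so that current treatment is examined on its own.
6. In Validity and reliability/rigour, state whether the stratified sampling phrase means stratified allocation, and reconcile it with the statement in Randomization and blinding that there are no stratification factors.

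The cost is wording changes, one extra form item, one extra model term and a less favourable statement of generalisability.
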